### 2.5. Sample Size and Power

Calculations to establish the sample size will be performed using RStudio 3.15.0 software (PBC, Boston, USA). The significance level will be set at *p* ≤ 0.05. According to the mean standard deviation established for VO_2max_ in a previous study [31] (SD = 1.5 mL/kg/min) and an estimated error (*d*) of 1.1, a valid sample size providing a 95% confidence interval (CI) in each group will be 7 (*n* = *CI*^2^ × *d*^2^/*SD*^2^). Thus, a final sample size of 7 for each group will provide a power of 93% if between and within a variance of 2.

### 2.6. Recruitment

Each club or association involved in athletics in Almería (Spain) will be screened to identify the percentage of high-level or professionally federated athletes. When there are at least 7 high-level or professionally federated athletes, the club/association officers will be contacted by telephone to inform them of the study objective. Once they agree, an informative talk will be carried out with the athletes and the coach to inform them of the study objective, the time period in which it will take place, and the required commitment by the athletes to measure their daily HRV according to the established protocol, to attend the pre and post-test sessions and to attend at least 90% of the training sessions. The coaches will be informed of the required commitment to adapt each athlete’s training session to the daily HRV score if their club is randomized into the HRV-G group. If they agree to participate, then they will have to sign the written consent and meet the eligibility criteria necessary to be recruited into the study. The recruitment process will be conducted by the trial steering members.

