Until just a few years ago, conducting research of this type, involving daily HRV measurements on each athlete and then adapting training based on these data, was only possible with the collaboration of high-cost laboratories. This study tests the use of noninvasive, commercial, low-cost and publicly accessible technology to evaluate the physiological responses obtained by adapting training to HRV.

Based on everything described above, we hypothesize that HRV-guided training will: (i) improve functional performance in high-level athletes and (ii) produce better performance results than a traditional training method. The objectives of the proposed protocol are: (i) to determine changes in the performance of high-level athletes after following an HRV-guided or a traditional training period, and (ii) to determine differences in the athletes’ performance after following both training protocols.

This will be a 12-week cluster-randomized controlled trial protocol in which professional athletes are assigned to either an HRV-based training group (HRV-G) or a traditional-based training group (TRAD-G). A block randomization method will be chosen to randomly assign participants to interventions in equally sized sample groups. This protocol has been designed following the Standard Protocol Items: Recommendations for Interventional Trials (SPIRIT) Statement [32]. To describe the intervention, the TIDieR (Template for Intervention Description and Replication) checklist by Hoffmann et al. [33] has been used.

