## 2. Materials and Methods

### 2.1. Study Setting

To detect an intervention-related effect in professional athletes, other studies with similar protocols [24,31] compared athletes from two clubs or associations. Similarly, our sample will comprise athletes from two sport institutions in Almería (Spain): the C.D. Atletas de Almería, based in the city of Almería (Spain) and the Asociación Espeleológica Velezana, based in Vélez Rubio (Spain).

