In accordance with Javaloyes et al. [24], all participants will be instructed to measure their HRV data at home each morning after waking up and emptying their bladders. They will be instructed to lie in a supine position and not perform any further activity during the recordings. Data will be recorded over a 60-s period e.g., [36]. The daily control and recording of the rMSSD, as well as the LnrMSSD_7-d_ calculation used to prescribe the training of the HRV-G athletes, will always be carried out by the trial steering members. These members will receive the information from each athlete via phone or email and, in turn, will inform the HRV-G coach of the training intensity corresponding to each athlete. This procedure will also serve as a strategy for maintaining and monitoring the athletes’ adherence to the training programs. Concomitant care, or any other intervention, will not be allowed during the trial for either the HRV-G or the TRAD-G. Athletes from both groups will carry out the training in their usual location.

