### 2.7. Allocation and Blinding

A block randomization method will be used to allocate participants to the groups, which will contain equal sample sizes. The block size will be determined by the data monitoring committee according to the statistical power provided. Blocks will be chosen randomly by tossing a coin to determine the participants’ assignment into the groups. This procedure will be carried out by the data monitoring committee. The athletes and the data monitoring committee will be blinded to the exercise group assignment.

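### The protocol names two units of randomisation; on the likelier one (clubs), each arm is a single club and the HRV effect cannot be separated from the club effect

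*Protocol article*

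**What the plan says.** Some statements point to randomisation of clubs:

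- Introduction (the Abstract uses the same label): "This will be a 12-week cluster-randomized controlled trial protocol in which professional athletes are assigned to either" one of the two training groups.
- Section 2.1: "our sample will comprise athletes from two sport institutions in Almería (Spain"). The two institutions are named and are based in different towns.
- Section 2.6: club officers are approached "When there are at least 7 high-level or professionally federated athletes". Coaches are told of their duty to adapt sessions to daily HRV "if their club is randomized into the HRV-G group".
- Section 2.3: the steering members "will inform the HRV-G coach of the training intensity corresponding to each athlete", with the coach in the singular. Also: "Athletes from both groups will carry out the training in their usual location".

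Others point to randomisation of athletes:

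- Section 2.7: "A block randomization method will be used to allocate participants to the groups, which will contain equal sample sizes". The data monitoring committee sets the block size, and "Blocks will be chosen randomly by tossing a coin".
- Introduction: a further sentence also has block randomisation assigning participants to equally sized groups.

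Section 2.5 sets 7 athletes per group with 93% power. Section 2.8 plans a t-test, or a Mann-Whitney test, on athletes.

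**The concern.** The unit of randomisation decides what the between-group comparison can show, and the protocol gives two answers. If athletes are randomised, the cluster label and the club clause in section 2.6 are wrong, and coaches are asked for the wrong commitment. If clubs are randomised and there are two, each arm is one club. Programme, coach and squad then change together.

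Objective (ii) is the difference in performance between the two programmes, and the Discussion expects it to favour HRV-G and to support HRV-guided training. With one club per arm, a positive result could equally reflect how one club's athletes progressed over the eight training weeks under their own coach. An unseen analysis plan could not repair this, because the data would hold no information on how much clubs differ in change when the programme is the same.

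**Working it through.** **1. The plan's own figures contain no cluster term.** Inputs from section 2.5: SD 1.5 mL/kg/min, error d = 1.1, 95% confidence (z = 1.96).

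- n = z² × SD² / d² = 1.96² × 1.5² / 1.1² = 7.14, about 7. This is the printed ratio turned over; as printed it gives 1.96² × 1.1² / 1.5² = 2.07.
- Power: a two-group one-way ANOVA with 1 and 12 df and a between/within variance ratio of 2 has noncentrality 7 × 2 = 14 and power 92.9%, matching the stated 93%. If both variances equal 2, power is 68.1%.

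Both reproductions treat the 14 athletes as independent. The formula and the variance wording are separate matters and do not affect this point.

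**2. How many clubs per arm?** No single sentence says. Two clubs (2.1), clubs randomised (2.6), a club minimum of 7 (2.6) equal to the group size of 7 (2.5), and one HRV-G coach (2.3) together give one club per arm.

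**3. Information at club level under that reading.**

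- Between-club df = clubs − arms = 2 − 2 = 0.
- There are 2 possible allocations, so the smallest two-sided randomisation p-value is 2/2 = 1.0.
- For comparison, 14 athletes randomised 7 v 7 have 3,432 possible allocations (smallest two-sided p = 2/3432 = 0.0006) and 12 df.

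**4. Type I error of an athlete-level test.** Assumptions: a two-sided, two-sample t-test on VO2max change, m = 7 per club, and a share ρ (the ICC) of the variance σ² of change lying between clubs.

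- True variance of the difference in means: 2σ²(1 + (m − 1)ρ)/m.
- Variance the t-test expects: 2σ²(1 − ρ)/m.
- The t statistic is therefore inflated by k = √[(1 + 6ρ)/(1 − ρ)], and the true type I error is 2 × P(t₁₂ > 2.179/k).

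| Assumed ICC of change | k | 2.179/k | True type I error |
|---|---|---|---|
| 0.01 | 1.035 | 2.106 | 5.7% |
| 0.05 | 1.170 | 1.863 | 8.7% |
| 0.10 | 1.333 | 1.634 | 12.8% |
| 0.20 | 1.658 | 1.314 | 21.3% |

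Recruiting more athletes from the same two clubs makes this worse: at an ICC of 0.05 the error is 13.1% with 14 per club and 30.0% with 50.

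**5. Illustration with the plan's numbers.** Take no HRV effect, but one club improving by 1.1 mL/kg/min more than the other, with 1.5 used as the SD of change (an assumption, since section 2.5 does not say it is one). The noncentrality is (1.1/1.5) × √(7/2) = 1.37, and the two-sided test is significant 24% of the time.

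**The case against.** **One club per arm is inferred.** This is true. Only section 2.6 says that a club is randomised, and the conclusion needs several sections read together. If section 2.7 governs and athletes are randomised, arm is no longer aliased with club and the type I figures fall away. If the blocks in section 2.7 are the clubs, the contradiction goes but the aliasing is confirmed. The text needs amending on either reading.

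**Design features reduce the threat.** Both groups share a four-week preparation period and the same eligibility criteria, one research group runs the treadmill test, and VO2max is measured before and after training. A reader might infer that any VO2max difference at the end could be a club difference. That goes too far, because a comparison of change removes stable differences between clubs. It does not remove a difference in how the clubs change during the training period.

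**The test is not clearly a two-sample test.** Section 2.8 says the t-test compares variables before and after the intervention, which can be read as paired within group. The figures above do not apply to a paired test. The Mann-Whitney fallback and objective (ii) make a between-group test plausible, but the figures depend on it.

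**Other studies compared two clubs.** Section 2.1 says so. Precedent does not make the effect identifiable.

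**Conclusion.** The contradiction over the unit of randomisation stands as written and must be resolved. The confounding is conditional: under club allocation, the likelier reading, arm is aliased with club and coach, between-club df are zero, and no analysis can separate a club-specific difference in change from an HRV effect. That conclusion needs no ICC.

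The range of 5.7% to 21.3% is secondary. It rests on club allocation, an athlete-level between-group t-test on change with 12 df, and an assumed ICC of change of 0.01 to 0.20. The protocol supplies no ICC. A reader might take these as the error rates of the trial as planned; the documents do not support that, because they settle neither the unit of randomisation nor the form of the test.

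**What to change.** State one unit of randomisation in the Abstract, the Introduction and sections 2.6 and 2.7.

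**Preferred: randomise athletes individually, stratified by club.** With 7 athletes from each club, allocate for example 4:3 in one and 3:4 in the other, giving 7 v 7, and adjust for club in the analysis. With that split fixed there are 35 × 35 = 1,225 possible allocations, and 14 − 3 = 11 residual df. Remove the cluster label from the Abstract and Introduction. In section 2.6 change only the clause "if their club is randomized into the HRV-G group", so that each coach still commits to adapting sessions for athletes allocated to HRV-G.

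Costs: no extra athletes, but a formal amendment, since section 2.10 requires one for a change of design. There will be some contamination between clubmates. Both coaches must agree to, and be briefed on, both programmes; the steering members already work out each athlete's HRV-guided intensity, but the protocol does not show that one coach can run both. The athlete blinding stated in section 2.7 also becomes harder to keep.

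**If club allocation is kept, or has already happened** (the protocol does not say): describe the study as a two-club comparison, state that club and programme effects cannot be separated, and withdraw the claim that a between-group difference is a randomised effect of HRV guidance. This costs only wording, but gives up the causal answer to objective (ii).

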### 2.7. Allocation and Blinding

A block randomization method will be used to allocate participants to the groups, which will contain equal sample sizes. The block size will be determined by the data monitoring committee according to the statistical power provided. Blocks will be chosen randomly by tossing a coin to determine the participants’ assignment into the groups. This procedure will be carried out by the data monitoring committee. The athletes and the data monitoring committee will be blinded to the exercise group assignment.

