### 2.2. Eligibility Criteria

The inclusion criteria for participating in the program will be: (i) to belong to the Spanish Athletics Federation; (ii) to have been training and competing in Spanish Athletics Federation competitions for at least two years; and iii) to be in the first third of the classification for the last five races of the previous season. Regarding the exclusion criteria, the following will be taken into account: (i) having cardiovascular pathologies, abnormal blood pressure parameters or diagnosed respiratory problems; (ii) being treated for psychological problems, or regularly taking a drug(s) that has a direct or indirect effect on the nervous system (e.g., anxiolytics, antidepressants or neuroleptics); (iii) substance use that is not permitted by the International Association of Athletics Federations (IAAF); (iv) occasional consumption of medication for a disease related to the cardiorespiratory system (e.g., influenza) that might alter performance and (v) not performing at least 90% of the workouts during the intervention.

The trial steering members will be responsible for checking that the subjects interviewed meet the inclusion criteria. The Spanish Athletics Federation’s medical team will certify that the subjects do not meet any of the exclusion criteria. After being informed of the study design and potential risks, all athletes will sign a written informed consent document. The model consent form is shown in Appendix A.

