The incremental treadmill test will be performed by the Physical Exercise and Human Performance Research Group at the University of Murcia (Spain). This is a more objective way of determining physical fitness and represents the maximal performance capacity of an individual [39]. First, with the athlete in the supine position, a cardiovascular examination will be carried out at rest by means of cardiac auscultation, blood pressure and an electrocardiogram (ECG). The electrodes for recording the ECG and heart rate will be kept in place throughout the test. The Cardioline Cube^®^ electrocardiograph will be used. To perform the incremental treadmill test, the Runner srl (Cavezzo Italy) treadmill will be used, as it was in other studies such as Ballesta-García, Martínez-González-Moro, Ramos-Campo, and Carrasco-Poyatos [40]. Similar to other studies, such as Nuuttila et al. [30] or Vesterinen et al. [31], a prior 2-min aerobic warm up will be performed at 6 km/h. The test itself will start at a velocity of 7 km/h. The speed will be increased by 0.1 km/h every 6 s. The incline will remain at 1% throughout the test. The athletes will be encouraged to perform at maximum effort. The test will end when the subject can no longer run; the subject will indicate this with a hand gesture. The recovery phase will then begin at 4km/h for 3 min followed by rest for a further 2 min. The tests will be considered maximal and valid when the theoretical heart rate (220-age) exceeds 85% and the respiratory exchange ratio (RER) is greater than 1.15 [41]. During the stress test, the subjects will breathe through a mask connected to a gas analyzer (Metalyzer 3b^®^, Cortex, Leipzig, Germany). All gas exchange parameters will be measured breath-by-breath and averaged every 30 s. The VO_2max_ will be defined as the oxygen consumption plateau [42]. The aerobic (VT1) and anaerobic (VT2) thresholds will be determined. Before each test, the gas analyzer will be manually calibrated. The test’s maximal speed (V_max_), maximal heart rate (HR_max_), and respiratory exchange ratio (RER) will be recorded. The V_max_ or HR_max_ will be defined as the highest speed, or heart rate, reached for a finished stage. The speed, heart rate, respiratory exchange ratio and VO_2_ at each ventilatory threshold will also be recorded as V_VT1,_ V_VT2_, HR_VT1_, HR_VT2_, RER_VT1_, RER_VT2_, VO_2VT1_, and VO_2VT2_, respectively. All tests will be carried out under similar environmental conditions (an ambient temperature of 20–22 degrees).

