### 2.9. Monitoring

A data monitoring committee will be set up during the study recruitment period. Interim analyses will be supplied to the committee in strict confidence, together with any other analyses that the committee may request. Based on the data monitoring committee’s advice, the trial steering members will decide whether or not to modify the trial intake.

In our study, an adverse event will be defined as any untoward medical occurrence in a subject without regard to the possibility of a causal relationship. Adverse events will be collected after the subject has provided consent and enrolled in the study. If a subject experiences an adverse event after the informed consent document is signed (entry) but the subject has not started to receive study intervention, the event will be reported as not being related to the study’s exercise program. For this study, the following will be considered serious adverse events: severe or permanent disability, use of prohibited substances and any other significant hazard as determined by the study members. Serious adverse events occurring after a subject has stopped participating in the study will not be reported unless the researchers feel that the event may have been caused by the study protocol procedure.

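### The blinding statement covers athletes, for whom it is not credible, and the committee that tosses the coin, and provides for no blinding of outcome assessors

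*Protocol article*

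**What the plan says.** All references are to the protocol article.

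- **Who is blinded (2.7).** "The athletes and the data monitoring committee will be blinded to the exercise group assignment". No other party is named.
- **Who allocates (2.7).** "Blocks will be chosen randomly by tossing a coin to determine the participants’ assignment into the groups", and then "This procedure will be carried out by the data monitoring committee". The committee also sets the block size.
- **What athletes know (2.2, 2.6).** "After being informed of the study design and potential risks, all athletes will sign a written informed consent document". An information talk for athletes and coach also covers the study objective. Coaches are told that they must adapt sessions to daily HRV "if their club is randomized into the HRV-G group".
- **What differs between arms (2.3).** TRAD-G follows a programme fixed in advance (Table 2). HRV-G sessions depend on the athlete's own HRV. Both arms record HRV at home every morning. The steering members do the calculation and pass the resulting intensity to the HRV-G coach.
- **How outcomes are obtained (2.4).** A University of Murcia group runs the treadmill test. "The athletes will be encouraged to perform at maximum effort", and the athlete ends the test by a hand signal. VT1 and VT2 are determined from the test. The 3000 m run is at maximum speed and is followed by a self-rated RPE.

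**The concern.** Blinding is a stated property of the design, and readers of the eventual report will rely on it. Here it is claimed for one party that performs the allocation and for another that lives with the intervention every day. The people for whom masking would be useful and perhaps achievable, those who run and read the tests, are not mentioned.

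Two things are at stake. First, the trial could be reported as participant-blinded when it is not. Second, several outcomes respond to how hard the athlete tries and how the tester behaves. If expectations differ between arms, part of an observed difference in 3000 m time, RPE, maximal treadmill speed or, to a lesser degree, VO2max could come from expectation and not from training.

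**Working it through.** The blinding statement contains no figure to reproduce. The check sets the passages side by side.

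**1. Committee.** One paragraph of 2.7 gives three facts: a coin toss decides the assignment; the committee carries out the procedure; the committee is blinded to assignment. Whoever carries out the toss sees its result, so the second and third facts conflict. This does not depend on the unit of allocation. If clubs are allocated, as 2.6 implies, then with the two clubs of 2.1 a single toss fixes every athlete's arm. If athletes are allocated in blocks, as 2.7 reads, the committee sees each block's result.

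Two other committee tasks do not create the conflict. Setting a block size ("The block size will be determined by the data monitoring committee according to the statistical power provided") reveals no one's arm. Receiving interim reports ("Interim analyses will be supplied to the committee in strict confidence") need not either, because reports can be coded.

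**2. Athletes.**
- They are told the design before consent (2.2), so they know what the two programmes are.
- One programme is fixed and the other varies from day to day and from athlete to athlete (2.3). An informed athlete can tell which one he or she is following.
- Under club allocation the HRV-G coach knows the arm, and the whole club shares it.
- Daily HRV recording is the same in both arms and tells the athlete nothing. The revealing element is the HRV-driven prescription.

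**3. Coaches and steering members.** The HRV-G coach receives each athlete's intensity and the steering members send it (2.3). Neither can be blinded, and the article does not claim that they are.

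**4. Assessors.** Section 2.7 names two blinded parties and stops. Sections 2.4 and 2.7 do not say whether testers know the arm. The accurate description is that no assessor blinding is provided for.

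**5. Which outcomes are exposed (2.4).**

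| Outcome | Route for bias | Safeguard in the text |
|---|---|---|
| VO2max | encouragement; athlete ends the test | plateau definition; RER above 1.15; heart rate above 85% of 220 minus age; calibrated analyser |
| Maximal treadmill speed | same | the RER and heart-rate criteria only |
| VT1, VT2 and derived values | reader's determination | none stated |
| 3000 m time and speed | maximal voluntary effort | none stated |
| RPE | self-rating | none stated |

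**6. Size.** The document gives no basis for the size of any bias. To show only how sensitive a small comparison would be, assume no true effect, a systematic difference b in VO2max between arms, independent athletes, and a two-sided two-sample t-test at 0.05 (sidedness is not stated). Take n = 7 per group and SD = 1.5 mL/kg/min from 2.5. The standard error is 1.5 × √(2/7) = 0.802, there are 12 degrees of freedom, and the noncentrality is b/0.802.

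| Assumed b (mL/kg/min) | Noncentrality | False-positive rate |
|---|---|---|
| 0 | 0 | 5.0% |
| 0.25 | 0.31 | 6.0% |
| 0.5 | 0.62 | 8.9% |
| 0.75 | 0.94 | 13.9% |
| 1.0 | 1.25 | 21.0% |

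Every nonzero b is an assumption. The table does not estimate what will happen in this trial.

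**The case against.** **Silence about testers is not a statement that they are unblinded.** This stands. The article is condensed, and the full protocol may contain masking procedures. A reader might infer that testers know the arm, but the text does not say so. What remains is that a section devoted to blinding names its blinded parties and leaves assessors out.

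**VO2max is protected.** This stands in part. The plateau definition and the RER and heart-rate criteria screen out clearly submaximal tests. They are thresholds, though: two tests can both pass with different effort. They do nothing for 3000 m time or RPE.

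**The committee could toss for coded labels.** That would reconcile the sentences, but 2.7 describes no coding. It says that the toss determines assignment into the groups.

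**Athletes might not recognise their arm.** The steering members do the calculation and the coach delivers the session, so certainty cannot be claimed for every athlete. With the design disclosed and the two programmes visibly different, blinding is still not a credible claim.

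**Interim looks.** Section 2.9 lets the steering members change the intake after committee advice, and significance stays at 0.05. A reader might infer that type I error is inflated by testing early and then extending recruitment. The document does not support that: it does not say that interim analyses test efficacy, or that intake would be extended after a non-significant result. It is no part of this point.

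**Independence of the laboratory.** A reader might infer that the treadmill group is external and can be masked at no cost. The article names the university but does not establish independence from the trial team, and it does not say who runs the 3000 m test.

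**Conclusion.** The point holds in three parts of unequal strength.

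- **Committee:** a direct contradiction within 2.7, independent of any assumption about the unit of allocation. Confidence is high.
- **Athletes:** the claim is not credible, given disclosure of the design and visibly different programmes. This rests on the reasonable assumption that informed athletes can tell a fixed plan from an HRV-driven one.
- **Assessors:** no blinding is provided for in the statement, while several outcomes depend on effort, self-rating or reading. This is a gap in the stated safeguards and no proof that testers know the arm.

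The resulting bias cannot be quantified from the document, and the illustrative false-positive rates hold only for the assumed biases. It would be too strong to say that bias acts unchecked on the primary outcome, because the validity criteria limit it. The correction should be made before results are reported: the present sentence describes a property that the design does not have.

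**What to change.** Revise 2.7 as follows.

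1. State that athletes, coaches and steering members are not blinded.
2. Have someone outside the data monitoring committee perform the allocation, or remove the claim that the committee is blinded.
3. State that, as far as practicable, the treadmill testers, threshold readers and 3000 m timers are masked. Give them coded IDs that show neither arm nor club, use a fixed script for encouragement, and instruct athletes not to disclose their arm.
4. If masking of any of these people is not practicable, say so.

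The cost is a revised paragraph, coded test lists and a short script, plus naming one person to allocate if that option is chosen. Whether the 3000 m test needs different staff cannot be judged, because the article does not say who runs it. The small downside is that with two clubs, and possibly one arm per club, a tester who recognises an athlete's club may infer the arm. Masking may therefore be imperfect and should be described that way.
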